## Assignment of interventions: blinding

### Who will be blinded {17a}

This is a single-blinded study. Practices are aware of their allocation to IG or CG and are therefore not blinded. Patients in the IG and CG will receive different study information to prevent unblinding on the patient side.

### Procedure for unblinding if needed {17b}

There is no structured procedure for unblinding defined as we do not expect the necessity for unblinding.

## Data collection and management

### Plans for assessment and collection of outcomes {18a}

We collect three different data types to evaluate the primary and secondary outcomes:
Medical data: HbA1c level (via LumiraDx HbA1c [34]), body composition (via Biody Xpert ZM II [35], blood pressure (via Omron M3 [36] either at the PCP’s practice or at a suitable location chosen by the patient in consultation with the study manager; prior fasting is not required) and antidiabetic drug use (number of DDDs) are measured at baseline, 12 and 18 months at the participating practices and are documented by the PCP or the study manager in the study software SOKLE. In the IG group, these variables are also collected within the 12 months intervention during regular PCP visits.Patient-reported data: PROMs (EQ-5D-5L, DIAB-Q, PHQ-9) and PREMs (Outpatient PREM questions—New South Wales government in Australia) are collected via the study software SOKLE. Patients receive PROM and PREM questionnaires via e-mail or SMS for self-administration. At baseline, manual completion (paper/pen) remains possible on request. The study manager is also available to help participants who encounter difficulties—however, the questionnaires are self-administered by the patients.Claims data: After completion of the study, Réseau Delta identifies patients insured with the Groupe Mutuel, and requests claims data (treatment, medication, etc.) from Groupe Mutuel via the insurance number of these patients (cf. Data management {19}). This data is matched to the patient pseudonym and securely transferred to the University of St. Gallen.

### Data management {19}

Standardized case report forms are implemented within the study software SOKLE to prevent typing errors and irrational value entries. The software will be used by authorized PCPs at the participating practices and the dedicated study manager. Where interoperable interfaces exist, entered personal and medical data from the participating practices is directly transferred to the study software. Otherwise, the study manager will enter the relevant personal and medical data into the study software manually. Data interactions within the study software are closely monitored and audited, with access restricted to authorized individuals only.

For patient-reported data (PROMs and PREMs), patients use a unique key for questionnaire completion, enhancing data confidentiality and integrity. Data will be pseudonymized in the study software. For adding claims data, patients sign a consent form that authorizes sharing of social insurance numbers with Groupe Mutuel. This allows Groupe Mutuel to identify the claims data of the respective patients. The claims data is then sent back to the Réseau Delta, who merges the claims data with the respective pseudonym.

Réseau Delta transfers pseudonymized project data for evaluation to the University of St. Gallen by secure transfer (SFTP server). Before the data is transferred to the University of St. Gallen, all participants’ identifying information is deleted. Hence, the University of St. Gallen is not able to identify any participant. All analyses will be conducted on a pseudonymized data set. Published evaluation reports will be completely anonymous. All study data must be retained by the study sites and the University of St. Gallen for at least 10 years following the completion of the trial.

### Confidentiality {27}

Data is stored on a server located in Onex (Geneva, Switzerland), in a Réseau Delta data center—a closed data center that is only accessible to authorized persons. Only an administrator, who has signed the confidentiality charter for access to Réseau Delta data, has access to the physical server for maintenance and monitoring. The administrator must carry an identity card, and access is recorded. All data is backed up daily. Each month, previous backups are moved to an external disk. Backups are encrypted using a key stored in a vault (HashiCorp vault). All software is subject to an annual security audit by a third-party company. All elements of the audit report are brought into compliance within days of the audit. Protection mechanisms against major threats are in place, notably those listed in the TOP 10 of the Open Web Application Security Project. Sensitive information is encrypted in the database (passwords, identification keys, access tokens, etc.). The database is not accessible from the outside.

### Plans for collection, laboratory evaluation, and storage of biological specimens for genetic or molecular analysis in this trial/future use {33}

Not applicable, as no biological specimens for genetic or molecular analysis are used.

## Statistical methods

### Statistical methods for primary and secondary outcomes {20a}

We will apply a range of statistical methods to evaluate our CRT.

#### Primary endpoint

HbA1c will be analyzed with common descriptive statistics, i.e., sample mean, median, minimum, maximum, standard deviation, and interquartile range. We will follow the intention to treat principle, i.e., all included patients who did not withdraw consent will be analyzed. We will apply two-sample (independent samples) t-tests or Wilcoxon-Mann–Whitney tests (depending on distribution) for the primary endpoint for the mean differences at baseline, month 12 and month 18 and changes in mean difference from baseline to 12 and 18 months. As we anticipate cluster effects at the practice level due to the randomization method, our main model for the assessment of the primary endpoint will be a mixed-effects model. We will control for patient characteristics at baseline (e.g., baseline HbA1c, BMI, gender, age, comorbidities, diabetes duration) as fixed effects, which are likely to affect the primary endpoint. In addition, we will incorporate practice as a random intercept in the model to account for potential cluster effects at the practice level. We will not control for covariate-restricted randomization variables, as differences between practices are accounted for by random intercepts. We use the Wald Test or the Likelihood Ratio Test to evaluate hypotheses on fixed and random effects.

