### Trial design {8}

The “Enhancing T2D Care” study is a two-arm multi-center cluster randomized controlled trial with a 1:1 patient allocation ratio and two parallel groups within a superiority framework [17]. Primary care physician (PCP) practices are randomized constrained for practice size, location, and specialization. As can be seen in Fig. 1, PCPs and associated healthcare professionals allocated to the intervention group (IG) will be trained on the TPE elements of the T2D program by professional educational patient therapists (TPE specialists) and on the utilization of PROMs within the program. Trainings will take place before enrollment of the first patient. The exact content of the training is described in the section Interventions.

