#### Secondary endpoints

Secondary endpoints (∆ EQ-5D-5L, ∆ DIAB-Q, ΔDDD ATC A10B, ∆ blood pressure, ∆ body composition, PREM) will be analyzed in a similar way taking into account different types of dependent variables and respective techniques, e.g., Wilcoxon-Mann–Whitney test for non-parametric data. Similar to the primary evaluation, the main model will be the mixed-effects model in which we will control for patient characteristics such as baseline outcome parameter value (e.g., EQ-5D-5L), BMI, gender, age and comorbidities as fixed effects, and incorporate clusters (practices) as random intercepts to also account for potential cluster effects. In addition, we will not control for randomization covariates. In analogue, we use the Wald Test or the Likelihood Ratio Test to evaluate hypotheses on fixed and random effects.

The cost-effectiveness analysis (CEA) will use ∆HbA1c as effect measure and costs evaluated from payer perspective including costs for all relevant treatments and drugs throughout the observed patient pathway at 12 and 18 months (see Appendix A, tab Groupe Mutuel). We further account for the cost of the intervention. The CEA will be performed in accordance with the consolidated standards for health economic evaluation reports (CHEERS 2022) [37]. The CEA will only be conducted for the participants that are insured at Groupe Mutuel due to data availability. In the case that the cost data are heavily right skewed, we will, as sensitivity analysis, perform a 95% winsorization on the cost data and repeat the CEA.

Analyses will be carried out using R, Stata, or Microsoft Excel as required.

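### The t-tests and rank tests planned beside the mixed model ignore practice, so they add invalid p-values of unstated status (about 6.7% real error for a nominal 5% at the planned ICC)

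*Protocol article*

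**What the plan says.** Under Trial design, the protocol article makes the practice the unit of randomisation: "Primary care physician (PCP) practices are randomized constrained for practice size, location, and specialization".

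The Primary endpoint section (Statistical methods) first lists descriptive statistics and then plans: "We will apply two-sample (independent samples) t-tests or" Wilcoxon-Mann–Whitney tests, the choice resting on the distribution. The comparisons are listed as "for the primary endpoint for the mean differences at baseline, month 12 and month 18 and changes in mean difference" to 12 and 18 months. Nothing adjusts these tests for practice, and nothing calls them descriptive or supportive.

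The next sentence says that cluster effects at practice level are expected and that "our main model for the assessment of the primary endpoint will be a mixed-effects model". That model has a random intercept for practice and fixed effects for baseline patient characteristics, including baseline HbA1c.

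The Secondary endpoints section says that these outcomes "will be analyzed in a similar way taking into account different types of dependent variables and respective techniques". It again names the Wilcoxon-Mann–Whitney test, and again names the mixed-effects model as the main one.

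**The concern.** The independent-samples t-test and the rank test both assume independent patients. When practices are randomised and patients within a practice resemble each other, the difference between arms varies more than these tests allow for, and their p-values are on average too small. The plan itself expects this dependence and pays for it in the sample size, then plans tests that leave it out.

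At stake is reporting. The 12-month change in HbA1c could appear with two p-values, one of them not valid under the design, and the plan does not say what the second is for. The same could happen for each secondary endpoint.

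**Working it through.** **Inputs** (Sample size section): difference 0.58 percentage points; SD 1.10; alpha 5% (sidedness is not stated, two-sided assumed); power 80%; ICC 0.032; mean cluster size 5; coefficient of variation (CV) of cluster size 0.30; dropout 15%. The 13 clusters are read as per arm, because only that reading leads to 77 per arm. A moderate correlation with practice attributes is also mentioned but given no value, so it is left out at first.

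**1. The plan's own sample size**
- Without clustering: 2 × [1.10 × (1.960 + 0.842) / 0.58]² = 56.5, so 57 per arm.
- Design effect: DE = 1 + [(1 + CV²) × m − 1] × ICC = 1 + (1.09 × 5 − 1) × 0.032 = 1.1424.
- With clustering: 56.5 × 1.1424 = 64.5 per arm; 64.5 / 5 = 12.9, so 13 practices and 65 patients per arm.
- Dropout: 65 / 0.85 = 76.5, so 77 per arm and 154 in total.

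The stated 154 is reproduced, and only with the clustering term. The sample size therefore assumes the dependence that the t-test and rank test ignore.

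**2. Error rate of the unclustered test at the planned ICC**
- Standard error: 1 − 1/√1.1424 = 0.064, so about 6% too small.
- Real two-sided error: 2 × [1 − Φ(1.96/√1.1424)] = 0.067, so 6.7% instead of 5%.
- Information: 130 analysed patients count as 130 / 1.1424 = 114.

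In 40,000 simulated null trials (13 + 13 practices, mean size 5, CV 0.30) the t-test rejected in 6.7% and the rank test in 6.5%. A size-weighted test on practice means with 24 degrees of freedom rejected in 5.0%. Smaller simulations gave 5.6% to 7.0% for the t-test.

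**3. Sensitivity**

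| Setting | DE | Real error of nominal 5% |
|---|---|---|
| ICC 0.032, planned sizes | 1.142 | 6.7% |
| ICC 0.032, 130 patients in 30 practices (m = 4.33) | 1.119 | 6.4% |
| ICC 0.032, balancing removes r² of the between-practice variance, r = 0.3 (assumed) | 1.127 | 6.5% |
| As above, r = 0.5 (assumed) | 1.099 | 6.2% |
| ICC 0.05 (assumed) | 1.2225 | 7.6% |
| ICC 0.08 (assumed) | 1.356 | 9.2% |

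The balancing rows use DE = (1 − 0.032) + 5.45 × 0.032 × (1 − r²). The ICCs of 0.05 and 0.08 are not in the protocol.

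**4. Disagreement between the two kinds of test**

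In the null simulation at ICC 0.032, the t-test and the practice-level test disagreed on significance in 2.9% of trials. At ICC 0 they disagreed in 2.5%. Clustering adds only about 0.4 percentage points; the rest comes from having two tests.

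**The case against.** The strongest reply is that the plan already says which analysis leads. Both endpoint sections name the mixed model as the main one, and the simple tests sit between the descriptive statistics and that model, so they read like an unadjusted first look. This stands. A reader might infer that the primary conclusion depends on an invalid test, and the text does not support that. What remains is that the tests are planned for the primary endpoint without a stated role.

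Second, the inflation is modest at the only ICC given, and it is smaller with around 30 practices or effective balancing. This also stands; the larger figures depend on assumed ICCs.

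Three further inferences are tempting but not supported:
- **That the t-test will give a smaller p-value than the main model.** The main model adjusts for baseline HbA1c and other covariates, so in a given dataset its p-value may be the smaller one. The unclustered p-value is too small relative to a cluster-aware test of the same contrast.
- **That comparing arms at baseline is pointless after randomisation.** Here practices know their allocation before they select and approach patients (Participant timeline, Allocation and Blinding sections). Baseline differences can reflect selection as well as chance, so they deserve description. The objection is only to unclustered p-values for them.
- **That "We use the Wald Test or the Likelihood Ratio Test to evaluate hypotheses on fixed and random effects" creates competing primary p-values.** The sentence covers both fixed and random effects, so it need not be a choice between two tests of the treatment effect. In simulations with 26 practices these tests ran at roughly 5.4% to 6.4%, depending on the variant. The choice of test and of degrees of freedom can be left to the analysis plan.

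**Conclusion.** The point holds as a fault in the supporting analyses. The planned t-tests and rank tests do not respect the randomisation by practice and conflict with the plan's own sample-size assumptions. At ICC 0.032 with about five patients per practice, a nominal 5% test has a real error of about 6.7%, or about 6.2% to 6.5% with smaller practices or some gain from balancing. This assumes a two-sided test, 13 practices per arm and an outcome ICC equal to the planning value; the error grows if the true ICC is higher. The main analysis accounts for practice, so the confirmatory result is not invalidated. The correction is worth making because the extra p-values are misleading and their role is open.

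**What to change.** In the Primary endpoint section, replace the unclustered tests with a cluster-aware unadjusted comparison: a mixed model with arm and a practice random intercept only, or a t-test on practice-level means. Alternatively, keep the simple comparison as description without p-values. Add one sentence stating that the covariate-adjusted mixed model alone decides the primary endpoint.

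Apply the same rule in the Secondary endpoints section. Report baseline differences between arms descriptively, without unclustered p-values.

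The change is to wording only and needs no further patients or data. The price is slightly wider unadjusted intervals. The study is expected to run until June 2027, so the text can be settled before the analysis.

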### Sample size {14}

The required sample size was calculated based on the expected effect size with respect to our primary endpoint and the specificities of CRTs [29]. We assume an effect size of 0.58 percentage point difference in change of HbA1c between baseline and 12 months in the IG compared to the CG. This assumption is grounded on results from studies with similar intervention designs (e.g., TPEs in individual and group sessions) [4, 6]. Expected distribution (measured by standard deviation) of the primary outcome at baseline is 1.10 [4]; the intraclass correlation is assumed to be 0.032 [30]. From our sample of participating practices, we expect an average size of the cluster of five eligible patients with a coefficient of variation of 30%. We use an a-priori matching before randomization to balance the sample on previously known practice attributes (urban vs. rural location, practice size, specialization of PCP)—we assume a moderate group-level correlation between practice attributes and change in HbA1c [31]. Assuming a commonly used Type 1 error rate (alpha) of 5% and aiming for a power of 80%, the trial requires a minimum of 13 clusters of five patients in each cluster. The sample size was estimated using the sample size calculator of the National Institute of Health [32]. Anticipating a drop-out rate of patients until the end of the trial period of 15% [4], we need to recruit a minimum of 154 patients (77 in the intervention group, 77 in the control group).

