## Assignment of interventions: allocation

### Allocation (sequence generation {16a}, concealment mechanism {16b}, and implementation {16c})

Balanced cluster randomization will be performed by a statistician at the University of St. Gallen who will not be involved in the recruitment or training of practices. Randomization will be based on previously known practice attributes (location, practice size, specialization of PCPs). We use covariate constrained randomization [33] to minimize imbalance from practice attributes. To this end, we employ the cvcrand command in Stata 18, performing 1000 randomizations, and select the allocation that best balances the covariates based on principal component analysis. A clustered permutation test (cptest) is done to test the performance of the randomization.

Group assignments will be implemented through a pre-prepared pseudonymized list of practices provided by Réseau Delta to the University of St. Gallen. Practices are then randomly allocated. The allocation of each of the practices to either intervention or control is marked down in this list, which is then sent back to Réseau Delta who will implement the allocation. The allocation sequence will be securely stored and concealed. The investigator—Réseau Delta—only receives a finalized version of the practice allocation list. Practices will only be informed of their allocation before patient inclusion starts (see Fig. 1). Practices will enter the study arm to which they have been randomly allocated.

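### The mixed models leave out the variables that constrain the randomisation on a mistaken rationale; the treatment standard error is somewhat too large, by a modest amount at the planned ICC

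*Protocol article*

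**What the plan says.** Three parts of the protocol article deal with the same practice attributes (location, practice size, specialisation) in different ways.

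- **Sample size {14}** describes a matching of practices before randomisation on these attributes and adds: "we assume a moderate group-level correlation between practice attributes and change in HbA1c". No value is given for that correlation.
- **Allocation {16a–16c}** describes something other than matching: "We use covariate constrained randomization [33] to minimize imbalance from practice attributes". Of 1000 candidate allocations, the one with the best balance is chosen.
- **Statistical methods {20a}, Primary endpoint** then leaves the attributes out of the analysis: "We will not control for covariate-restricted randomization variables, as differences between practices are accounted for by random intercepts". The Secondary endpoints text repeats this: "In addition, we will not control for randomization covariates".

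The primary model does include patient-level covariates, baseline HbA1c among them, and a random intercept for practice. Hypotheses are tested by Wald or likelihood ratio test, and no small-sample reference distribution is named.

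**The concern.** The exclusion is a stated decision with a stated reason, so it is not a detail left to an analysis plan. The reason confuses two things. A random intercept models how much practices vary. It does not adjust the treatment comparison for measured attributes that explain part of that variation.

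This matters because the randomisation is constrained. Choosing a well-balanced allocation lowers the true sampling variance of the treatment estimate to the extent that the attributes are prognostic. A model without the attributes cannot see this reduction: it leaves the balanced component in the practice variance and carries it into the standard error. The design gains precision that the analysis does not report.

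At stake are a standard error that is too large, some power given up although the data are already held, and a sample size section that names a correlation the planned analysis does not use.

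**Working it through.** **Inputs, all from Sample size {14}.** Difference 0.58 ("We assume an effect size of 0.58 percentage point difference in change of HbA1c between baseline and 12 months"); SD 1.10 ("Expected distribution (measured by standard deviation) of the primary outcome at baseline is 1.10"); ICC 0.032 ("the intraclass correlation is assumed to be 0.032"); cluster size 5 and coefficient of variation 0.30 ("we expect an average size of the cluster of five eligible patients with a coefficient of variation of 30"% in the text); alpha 5%, taken here as two-sided; power 80%; drop-out 15%. Not given: the practice-level correlation r. I read moderate as r = 0.3 to 0.7, so that the attributes explain r² of the between-practice variance.

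**1. The plan's own figure, with no allowance for the attributes.**
- Individual randomisation: n per arm = 2 × (1.96 + 0.8416)² × 1.21 / 0.3364 = 56.5.
- Design effect: 1 + ((1 + 0.09) × 5 − 1) × 0.032 = 1.1424.
- 56.5 × 1.1424 = 64.5 per arm, or 12.9 practices, rounded up to 13 (65 patients).
- 65 / 0.85 = 76.5, rounded up to 77 per arm, 154 in total.

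The stated 13 practices (per arm) and 154 patients are reproduced with no allowance at all.

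**2. Power at 13 practices per arm.** Between-practice variance is 0.032 × 1.21 = 0.0387; within-practice variance is 0.968 × 1.21 = 1.1713.
- SE = √(2 × (1.1713 + 1.09 × 5 × 0.0387) / 65) = 0.2062, and 0.58 / 0.2062 = 2.81.
- Normal approximation: 80.3%. With t on 2 × 13 − 2 = 24 df: 77.0%. Both figures take no allowance, so the gap between them is due only to the reference distribution.
- If the between-practice variance is multiplied by (1 − r²): 77.6%, 78.6% and 80.1% at r = 0.3, 0.5 and 0.7 on 24 df. With three covariates in the model (21 df): 77.1%, 78.1% and 79.6%.
- If instead baseline HbA1c explains 10% of within-practice variance (an assumption): SE = √(2 × (1.0542 + 0.2110) / 65) = 0.1973, and power is 80.5% on 24 df with no allowance for practice attributes.

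**3. How much too large is the standard error?** With equal practices of five and near-perfect balance, in units of total variance, a practice mean has variance 0.968/5 + 0.032 = 0.2256. The part that truly affects the balanced comparison is 0.1936 + 0.032 × (1 − r²). The ratio of standard errors is the square root of the quotient; for r = 0.7 it is √(0.2256 / 0.2099) = 1.037.

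**4. Simulation.** 26 equal practices of five, three practice covariates, best of 1000 allocations, t reference, practice-level analysis standing in for the random-intercept model, 120,000 data sets per setting. With the covariates included, type I error was about 5.0% throughout.

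| r | SE ratio (step 3) | Type I error, omitted | Power, omitted | Power, included |
|---|---|---|---|---|
| 0.3 | 1.006 | 4.9% | 77.4% | 77.0% |
| 0.5 | 1.018 | 4.7% | 77.7% | 78.1% |
| 0.7 | 1.037 | 4.3% | 77.8% | 79.4% |
| 1 (bound) | 1.079 | 3.6% | 78.8% | 82.7% |

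With a cut-off of 1.96 and the covariates omitted, type I error is 6.0%, 5.7% and 5.4% at r = 0.3, 0.5 and 0.7.

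**5. Sensitivity.** With 30 practices and half of the between-practice variance explained, at ICC 0.032: type I error 3.9% omitted against 4.8% included, power 80% against 82%. At ICC 0.10, which is an assumption about three times the plan's value: 3.4% against 5.2%, and 71% against 77%. Step 3 agrees in direction: at ICC 0.10 and r² = 0.5 the ratio is √(0.28 / 0.23) = 1.103.

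**The case against.** The best defence is that little is lost. Leaving out balanced practice covariates does not bias the treatment estimate. At ICC 0.032 and five patients per practice, between-practice variance is only 0.032 / 0.2256 = 14% of the variance of a practice mean, so there is not much to recover. If the attributes are weakly prognostic (r = 0.3), adding them costs slightly more in degrees of freedom than it gains. All of this stands.

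Two stronger readings are tempting, and the article supports neither.

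- *The trial loses its 80% power through the omission.* The 13 practices per arm are reproduced with no allowance. The fall from 80.3% to 77.0% comes from moving from a normal to a t reference. Adding the covariates does not by itself bring power back to 80% for r up to 0.7, and adjustment for baseline HbA1c, for which the sample size section states no allowance, could close the gap. The article does not report r or how its calculator used it, so any dependence of the sample size on the attributes is unreported rather than shown.
- *The planned test is conservative.* That holds only with a small-sample reference. With the Wald test as named and a cut-off of 1.96, type I error is about 5 to 6%, because the small number of practices pushes it up while the omission pushes it down.

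Neither point rescues the rationale. Two errors pulling in opposite directions are no reason to keep either, and the three sections still do not agree.

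**Conclusion.** The point holds as a correctable flaw in the analysis and an inconsistency between sections. The stated reason for leaving out the constraining variables is incorrect, and the model-based standard error is somewhat too large whenever those variables predict HbA1c change, which the sample size section itself assumes.

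On the plan's inputs the standard error is about 1 to 4% too large for r of 0.3 to 0.7. With a t reference, type I error is about 4 to 5% and the power given up is about 0 to 2 points. The loss grows with a higher ICC or r.

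These sizes rest on an assumed range for r, a two-sided 5% test, equal practice sizes in the simulation, and a practice-level analysis standing in for the mixed model. This should be corrected, but it does not threaten the validity of the trial.

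**What to change.** - **Primary and secondary models {20a}:** delete the rationale sentence and its counterpart for secondary endpoints. State instead that location, practice size and specialisation enter as fixed effects alongside the patient covariates and the random practice intercept, and name a small-sample reference distribution for the treatment effect.
- **Alternative:** a permutation test within the constrained set of allocations. This needs a defined and stored set of acceptable allocations; the Allocation section describes taking the single best of 1000 and mentions a permutation test only as a check of the randomisation. Fixed effects are the simpler route.
- **Sample size {14}:** replace the reference to matching with covariate-constrained randomisation and a covariate-adjusted analysis. Either state the correlation that was assumed and how the calculator used it, or state that no allowance was taken.

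The cost is wording and about three practice-level degrees of freedom (24 to 21 with 26 practices), more if specialisation has over two categories. If the attributes are weakly prognostic, the power loss is negligible (77.4% to 77.0% at r = 0.3). No new data are needed, since the attributes are known from randomisation. The change should be made before outcome data are analysed; the Trial status section expects the study to run until June 2027.

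### The test of the treatment effect is left open between Wald and likelihood ratio; in their usual large-sample forms these differ with 26 to 30 practices, and some permitted choices modestly exceed 5%

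*Protocol article*

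**What the plan says.** The Primary endpoint section under Statistical methods {20a} makes a mixed-effects model with a random intercept per practice the main analysis. It adjusts for an open-ended list of about six patient characteristics. On testing it says: "We use the Wald Test or the Likelihood Ratio Test to evaluate hypotheses on fixed and random effects". The Secondary endpoints section repeats the choice: "we use the Wald Test or the Likelihood Ratio Test to evaluate hypotheses on fixed and random effects".

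Neither section says which test decides. Neither gives the estimation method (ML or REML), the reference distribution or the degrees of freedom.

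The error rate is fixed elsewhere. Sample size {14} reads: "Assuming a commonly used Type 1 error rate (alpha) of 5% and aiming for a power of 80" (per cent), with a minimum of 13 clusters of five. Study setting {9} expects about 30 practices. Trial design {8} describes "two parallel groups within a superiority framework".

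**The concern.** Two tests of one hypothesis joined by *or* is a statement, not a silence: the confirmatory p-value can come from either. With many practices this would hardly matter. With 26 to 30 practices and several covariates, the familiar forms (Wald z, and likelihood ratio against chi-square) do not coincide, and neither is guaranteed to hold 5%.

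A likelihood ratio test of a fixed effect also requires ML rather than REML, and ML understates the variance. At stake are whether the 5% in the sample size is what the analysis delivers, and whether the result could turn on a test picked after the data are seen.

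**Working it through.** **1. The plan's own figure.** Inputs from Sample size {14}:
- Effect: "We assume an effect size of 0.58 percentage point difference in change of HbA1c between baseline and 12 months".
- SD: "Expected distribution (measured by standard deviation) of the primary outcome at baseline is 1.10".
- ICC: "the intraclass correlation is assumed to be 0.032".
- Clusters: "we expect an average size of the cluster of five eligible patients with a coefficient of variation of 30" (per cent).

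The calculation:
- Independent patients per arm: 2 × (1.10 × (1.960 + 0.842) / 0.58)² = 56.5.
- Design effect: 1 + ((1 + 0.30²) × 5 − 1) × 0.032 = 1.1424.
- 56.5 × 1.1424 = 64.5 patients, or 12.9 clusters of five, so 13 per arm (65 patients).
- 65 / 0.85 = 76.5, so 77 per arm and 154 in total.

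This reproduces the plan, with 13 read as per arm (26 in all) and a two-sided 5% test. Sidedness is not stated, but a one-sided test needs only about 51 patients (11 clusters) per arm.

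**2. A rough check.** If the test statistic behaves like t on (practices − 2) degrees of freedom, using 1.96 rejects 6.2% of the time on 24 df and 6.0% on 28 df. ML adds to this. With 126 patients and 8 fixed effects (intercept, arm, six covariates), its residual variance is smaller than the REML value by the factor 118/126 at a given ICC, so the standard error is about 3% smaller.

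**3. Simulation under no effect.** Random-intercept model, 20,000 trials per setting (Monte Carlo SE about 0.15 points), six covariates. Practice sizes run from 3 to 7, a CV of about √(10/7)/5 = 24%, somewhat below the plan's 30%. The size pattern and covariate count are assumptions. Type I error at ICC 0.032:

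| Test | 26 practices | 30 practices |
|---|---|---|
| ML Wald z | 6.5% | 6.2% |
| Likelihood ratio, chi-square 1 df | 6.0% | 5.5% |
| REML Wald z | 5.5% | 5.1% |
| REML t, practices − 2 df | 4.3% | 4.2% |

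Without covariates the first three rows are 5.8%, 5.2% and 5.2% (26 practices) and 5.6%, 5.0% and 5.1% (30 practices).

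**4. With the constrained randomization.** A separate run (26 practices, six covariates, ICC 0.032, 6,000 trials, SE about 0.3 points) compared simple allocation with the best of 1000 allocations:

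| Test | Simple | Constrained |
|---|---|---|
| ML Wald z | 6.2% | 6.0% |
| Likelihood ratio | 5.6% | 5.4% |
| REML Wald z | 5.0% | 5.0% |
| REML, Satterthwaite df | 4.4% | 4.4% |

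**5. Disagreement.** At ICC 0.032, ML Wald z and likelihood ratio gave opposite verdicts in 0.5-0.7% of null trials. In every one, only Wald was significant. Taking whichever of the two rejects therefore gives exactly the ML Wald rate.

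**6. Sensitivity to the ICC (assumed values), simple allocation, six covariates.** At ICC 0, ML Wald z is 5.2-5.5% and likelihood ratio 4.7-5.0%. At ICC 0.10 they are 6.9-7.5% and 6.1-6.7%.

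**7. Power with a t reference.** At 13 clusters of five per arm the standard error is 1.10 × √(2 × 1.1424 / 65) = 0.206, and 0.58 / 0.206 = 2.81. Power is 80.3% against 1.96 and 77.0% against t on 24 df (critical value 2.06). With 14 clusters of five per arm it is 80.2%. No credit is taken for the matching, because the protocol gives no value for its correlation.

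**The case against.** The strongest reply is that the protocol never says the tests are large-sample ones. A REML t or F test of the treatment coefficient is itself a Wald test, so the remedy already falls within the printed sentence. Estimation method and degrees of freedom are details that an analysis plan, not shown here, may well settle. This stands: a reader might infer that the protocol commits to tests known to be too liberal, and the text does not support that. It does not answer the open choice between two tests, and the likelihood ratio option has no comparable small-sample reading.

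Second, the design itself lowers the rejection rate, because practices are balanced on attributes that the model then omits. Further simulations assumed that those attributes explain 25% or 50% of the between-practice variance. At ICC 0.032 they gave 5.4-5.8% for ML Wald z, 4.9-5.3% for likelihood ratio and 4.4-4.8% for REML Wald z. If the attributes are that prognostic, only ML Wald z stays above 5% by more than simulation error. The protocol gives no such share, so this bounds the excess from below rather than removing it.

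Third, one could read the sentence as prescribing a Wald test of the practice variance, whose null value lies on the boundary of the parameter space. The sentence lists two tests and two kinds of effect without pairing them. Likelihood ratio for the variance and Wald for the coefficient is just as natural a reading, so that charge is not made here.

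**Conclusion.** The point holds as one of wording with a modest statistical consequence. Two tests are allowed for the primary hypothesis and nothing in the protocol selects one. At the plan's ICC with six covariates, the usual large-sample forms give about 6.0-6.5% (ML Wald z), 5.4-6.0% (likelihood ratio) and 5.0-5.5% (REML Wald z). Those ranges span 26 and 30 practices and include the run with constrained allocation at 26. Between ML Wald and likelihood ratio, a later choice can only add significant results.

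A reader might go further and infer that the 5% level is badly breached. The documents do not support that. Rates near 7% and above need an ICC around 0.10, about three times the stated 0.032 and given nowhere in the protocol, or a longer covariate list (6.9% for ML Wald z with ten). With an ICC near zero or no covariates the excess shrinks, and for the likelihood ratio and REML Wald z tests it nearly vanishes. The figures rest on the assumed practice sizes and covariate count, and on normally distributed outcomes.

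**What to change.** Replace the testing sentence in the Primary endpoint and Secondary endpoints sections with one rule for the treatment effect in the linear mixed models. Fit by REML, and use a two-sided 5% t or F test with one named degrees-of-freedom method (Satterthwaite or Kenward-Roger) and the confidence interval from the same method. Report the practice variance and ICC descriptively, without a test.

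The cost is a change of wording. The study runs to June 2027 with no formal interim analysis, so the change can be made before 12-month results are analysed.

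There are two downsides to record. At a low ICC the rule is slightly conservative: about 4.4% with Satterthwaite (Kenward-Roger was not simulated). Power falls a little: at worst from 80.3% to 77.0% at 13 clusters of five per arm with t on 24 df, and less with Satterthwaite degrees of freedom. Intervals widen by at most 2.06 / 1.96, about 5%. Sample size {14} should acknowledge this next to its 80%. Fourteen practices per arm with five analysed patients each would restore 80.2%, which is within the roughly 30 practices planned if each reaches that number.
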